##### Sample size justification

We expect to collect mental health data from at least 52 clients in each of the 15 centers (*N* = 780). Power was computed to test the null hypotheses of no difference in outcomes between Materials Only and Direct Training and between Direct Training and Local Supervision in a cluster randomized trial. The standardized change in the primary outcomes (PHQ-9) over 8 months was estimated as 0.92 (est. = −0.79 [0.74]), for Local Supervision, the strategy used in a randomized controlled trial in which LGBTQ-affirmative CBT study therapists received ongoing supervision [48]. With a 0.05 Type I error rate, we have 80% power to detect an effect size of *d* = 0.33–0.37 for 8-month change, assuming a between-center ICC as large as 0.01 and loss to follow-up of 25%. In other words, we will have 80% power to detect the difference between Direct Training and Local Supervision when the standardized change for Direct Training is at most 0.55–0.59. Further, assuming that the standardized change in the outcome is 0.54 for Direct Training, we have 80% power to detect the difference between Materials Only and Direct Training when the standardized change in PHQ-9 is 0.18–0.26 or less for Materials Only.

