#### Provider implementation fidelity outcome analyses

We will summarize provider characteristics (e.g., volunteer status, length of SGM service) overall and by implementation strategy and assess for baseline imbalances. We will then compare the implementation outcomes for the Materials Only condition vs. Direct Training vs. Local Supervision. The primary implementation outcome is provider implementation fidelity (assessed via simulated practice responses) at 8-month follow-up; secondary outcomes include 8-month provider self-efficacy, competency, familiarity, and use of LGBTQ-affirmative CBT. For primary and secondary outcomes, will use mixed effects models [93] with the identity link function to compare the effect of implementation strategies. The fixed effects include the time effect and the time × implementation strategies interaction terms; the random effects include center and within-provider repeated measures. We will use the robust score test to assess whether the interaction terms are significantly different across the three strategies, with a 0.05 overall Type I error rate, and a 0.025 error rate for each of the two primary strategy comparisons. For secondary outcomes, we will compare implementation strategies with a 0.05 Type I error rate. We will re-run these analyses with 12- and 24-month outcomes to determine implementation maintenance.

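### Aim 3's Materials Only threshold of 0.18–0.26 does not follow from the plan's own inputs, which give 0.17–0.21, and the alpha behind the detectable effect needs stating

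*Protocol article*

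**What the plan says.** The client-outcome paragraph (Protocol article, Effectiveness outcome analysis, Sample size justification) covers two contrasts: Materials Only against Direct Training, and Direct Training against Local Supervision. Its inputs and claims are:

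- Sample: "We expect to collect mental health data from at least 52 clients in each of the 15 centers", 780 in total. The Background section puts five of these centers in each condition.
- Error rate and power: the claim opens "With a 0.05 Type I error rate, we have 80% power to detect an effect size of" a given magnitude.
- Detectable effect: that magnitude is put at 0.33–0.37 on the change at 8 months.
- Clustering and attrition: the figures are given "assuming a between-center ICC as large as 0.01 and loss to follow-up of 25" percent.
- Local Supervision is taken at a standardized change of 0.92. The contrast with Direct Training is said to have 80% power if Direct Training is at most 0.55–0.59.
- Direct Training is then set at 0.54. The contrast with Materials Only is said to have 80% power "when the standardized change in PHQ-9 is 0.18–0.26 or less for Materials Only".

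For the same two contrasts on provider fidelity, the Aim 1 analysis section sets 0.05 overall and "a 0.025 error rate for each of the two primary strategy comparisons". The Aim 1 power calculation also uses 0.025. The Effectiveness outcome analysis section names PHQ-9 at 8 months as the primary effectiveness outcome but gives no alpha for its two contrasts. The 0.05 stated there is for secondary outcomes.

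**The concern.** Each threshold in the power paragraphs should be an assumed change minus (or plus) the detectable effect. The Materials Only threshold is not. It is too generous at its upper end, so a reader would believe that the trial can separate Direct Training from Materials Only in a situation where the plan's own figures say it cannot with 80% power. With only five centers per condition, that affects how a null result on this contrast is read.

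The two aims also treat the same pair of contrasts under different error rates without a stated reason, so it is unclear which error rate the detectable effect of 0.33–0.37 refers to.

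**Working it through.** **1. The plan's own method, where it works.**

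- Aim 3, Local Supervision line: 0.92 − 0.37 = 0.55 and 0.92 − 0.33 = 0.59. This matches the stated 0.55–0.59.
- Aim 1, d = 0.34–0.46 around 0.67: 0.67 − 0.46 = 0.21, 0.67 − 0.34 = 0.33, 0.67 + 0.34 = 1.01, 0.67 + 0.46 = 1.13. All four match the stated limits.

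**2. The same method on the Materials Only line.**

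- 0.54 − 0.37 = 0.17 and 0.54 − 0.33 = 0.21, against the stated 0.18–0.26.
- The lower end is off by 0.01, which could be rounding. The upper end is off by 0.05, which could not.
- 0.55 − 0.37 = 0.18 and 0.59 − 0.33 = 0.26 reproduce both printed ends exactly.

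**3. Power at the printed upper end.** The difference is 0.54 − 0.26 = 0.28. At two-sided 0.05 and 80% power, z(0.975) + z(0.80) = 1.960 + 0.842 = 2.802, so power = Φ(2.802 × 0.28 / d − 1.960).

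- If d = 0.33: Φ(0.417) = 66%.
- If d = 0.37: Φ(0.160) = 56%.

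Direct calculation, assuming two-sided testing and 52 × 0.75 = 39 analysed clients per center:

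- n per arm = 5 × 39 = 195.
- Design effect = 1 + 38 × 0.01 = 1.38.
- SE = √(2 × 1.38 / 195) = 0.119.
- Power = Φ(0.28 / 0.119 − 1.960) = 65%.
- With a t reference distribution it is lower: 54% on 8 df (two arms) or 58% on 12 df (15 centers less 3 arms).

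At the printed lower end the difference is 0.54 − 0.18 = 0.36. Power is 78% if d = 0.37 and 86% if d = 0.33, so that end does no harm.

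**4. Which alpha lies behind 0.33–0.37?** Detectable d = (z(1 − α/2) + z(0.80)) × SE, with the inputs of step 3.

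| ICC | Reference | α = 0.05 | α = 0.025 |
|---|---|---|---|
| 0 | normal | 0.284 | 0.312 |
| 0.01 | normal | 0.333 | 0.367 |
| 0 | t, 8 df | 0.324 | 0.373 |
| 0.01 | t, 8 df | 0.381 | 0.438 |

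At α = 0.05 the normal formula never exceeds 0.333 for ICC up to 0.01. The two stated ends coincide with the normal results at ICC 0.01 for 0.05 and 0.025. With 12 df the 0.05 range is 0.31–0.36. None of these settings at 0.05 gives exactly 0.33–0.37. The paragraph does not say what was varied, so the alpha cannot be settled from the text.

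**5. Error rate with no split.** Two contrasts at two-sided 0.05 sharing the Direct Training arm have correlation −0.5. The simulated chance of at least one false rejection in either direction is 9.1% (9.75% if they were independent). The chance of falsely declaring that a more intensive strategy is better is about 5.0%: 0.025 + 0.025, with almost no overlap.

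**The case against.** The threshold is interpretive. It sets neither the 15 centers nor the 780 clients, and the stated d does not depend on it. PHQ-9 is the primary outcome of one aim in a trial whose primary outcome is provider fidelity, so a different error convention there may be deliberate, and its detail may sit in an analysis plan that is not shown. All of this stands and limits the size of the point. It does not rescue the printed range, because the conflicting figures stand in one paragraph.

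A reader might infer more than the document supports:

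- **That the center ICC was left out at the favorable end.** The implied 0.28 is close to the unclustered 0.284. This explains one end only, whereas the carry-over from 0.55–0.59 explains both.
- **That both primary PHQ-9 tests will be run at 0.05.** Only the power sentence says 0.05. The analysis section gives no alpha for them and also plans a test across all three strategies. If the pairwise tests were conditional on it, simulated error under the global null would be about 4%. The text does not say that they are.
- **That there is a 9% chance of a false client-benefit claim.** The 9% counts both directions; a false benefit claim has about 5%.
- **That Aim 1 needs another procedure, such as Holm.** Its 0.025 split already controls 5% and matches its power calculation.
- **That the stated d is optimistic once between-center degrees of freedom are used.** This depends on the choice: 0.381 at 8 df, but about 0.36 at 12 df, for ICC 0.01.

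**Conclusion.** The Materials Only threshold is wrong as written. Given 0.54 and d = 0.33–0.37 it is 0.17–0.21, and this needs no assumption beyond the plan's printed figures. At the printed limit of 0.26, power is 56–66% scaled from the stated d, or 65% by the normal formula with 39 analysed clients per center, ICC 0.01 and two-sided 0.05. The carry-over from 0.55–0.59 is the likeliest source, but it is an inference.

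The alpha point is secondary. The Aim 3 power calculation uses 0.05 where Aim 1 uses 0.025 for the same contrasts, no reason is given, and the alpha behind 0.33–0.37 is unclear. That is an ambiguity to resolve and not proof of uncontrolled testing.

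**What to change.** 1. Reconcile 0.54 with 0.55–0.59. If 0.54 stands, print 0.17–0.21. If Direct Training was meant to sit at its own limits of 0.55–0.59, replace 0.54 with that range and say that the ends are paired (0.55 with d = 0.37, 0.59 with d = 0.33). In that case 0.18–0.26 is correct.
2. State which alpha, which ICC values and how many analysed clients per center lie behind 0.33–0.37.
3. State the error rate for the two PHQ-9 contrasts. If the 0.05 overall rule of Aim 1 is meant to apply, use 0.025 each and restate d: about 0.37 at ICC 0.01 by the normal approximation, and larger with between-center degrees of freedom (0.438 at 8 df). Rescaling the stated range by (2.241 + 0.842) / 2.802 = 1.10 gives about 0.36–0.41, and a Materials Only threshold of about 0.13–0.18 from 0.54. If 0.05 per contrast is intended, say so and give the reason.

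The cost is a few lines of text and a somewhat less favorable power statement. The design, the sample size and Aim 1 do not change.

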#### Mediation analyses

We will assess client mental health as a function of our three implementation strategies as mediated through provider and organizational targets. We hypothesize that organizational (e.g., norms about LGBTQ-affirmative CBT) and provider (e.g., LGBTQ-affirmative CBT self-efficacy) targets will mediate the impact of implementation strategies on implementation success, and further on client mental health. We will use the difference approach [101] for multilevel mediation [102] of center-level implementation strategy on 8-month follow-up provider-level implementation fidelity through our hypothesized organizational and provider targets measured at 4-month follow-up. We will parse the implementation strategies’ total effect on the implementation outcome into direct and indirect (mediated) effects. Specially, we will fit a mixed-effects model of the implementation strategies on implementation outcome for the total effect and fit another mixed-effects model of the implementation strategies on implementation outcome plus center-level targets and provider-level targets. The fixed effects of the first model include the implementation strategies, baseline implementation fidelity, and baseline organizational and provider targets, and the second model replaces baseline organizational and provider targets with 4-month follow-up targets; random effects include center. The indirect effect is the difference between the estimated coefficients of implementation strategies between the two models; significance will be tested using bootstrapping [103]. We will use the same multilevel approach to test mediation of the association between implementation strategy and 12-month follow-up client-level PHQ-9. We will fit two mixed-effects models to estimate the total, direct and indirect (mediated) effects. The fixed effects of the first model include the implementation strategies, baseline PHQ-9, baseline implementation fidelity, and baseline organizational and provider targets, and in the second model, the baseline organizational and provider targets are replaced with 4-month follow-up targets and baseline implementation fidelity is replaced with 8-month follow-up implementation fidelity; the random effects include center and provider. We will re-run these analyses with 24-month follow-up PHQ-9 to determine maintenance of effects.

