**Methods:**

This hybrid type III effectiveness-implementation trial will randomize 90 centers to receive one of three additive strategies for implementing LGBTQ-affirmative CBT: [1] a suite of self-paced digital learning materials (Materials Only condition); [2] these materials plus weekly live webinar training for 12 weeks (Direct Training condition); or [3] the above plus one year of supervision from a local supervisor who will receive expert consultation in a train-the-trainer format (Local Supervision condition). The primary outcome will be provider fidelity assessed via simulated practice. Implementation determinants (e.g., center resources, provider/client characteristics), mediators (e.g., implementation climate, provider self-efficacy), and other outcomes (e.g., intervention adaptation, sustainment) will be captured using a mixed-methods design. Clinical effectiveness outcomes (i.e., client mental and behavioral health symptoms) will be assessed through client surveys among a subset of 15 centers.

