We hypothesize that these three additive training implementation strategies will predict respective graduated increases in implementation success at 4-, 8-, 12-, and 24-months post-training (see Figs. 1 and [67]). That is, we predict that reach, effectiveness, adoption, implementation, and maintenance will be higher in the Local Supervision condition relative to the Direct Training condition and that the Direct Training condition’s implementation outcomes will be higher than the Materials Only condition. Drawing on theories of organizational [68, 69] and provider [70–73] change, we also hypothesize that organizational (e.g., shared norms of the importance of EBP) and provider (e.g., self-efficacy for EBP delivery) factors will mediate the stronger impact of the more intensive training strategies on implementation success and client mental health outcomes. To facilitate this latter aim, in a subset of 15 LGBTQ community centers (five centers per condition), we will compare the three training implementation strategies in terms of client mental health symptom change from before implementation to 4, 8, 12, and 24 months after.

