#### Mental health providers

Following randomization, mental health providers working at or affiliated with enrolled LGBTQ community centers will be invited to register for the training. Eligible providers must (1) be 18 years or older; (2) provide or be planning to provide mental/behavioral health services (e.g., therapy, support groups, case management) to LGBTQ clients; and (3) be affiliated with an enrolled LGBTQ community center. In order to meet the third criterion, providers may either be employed or volunteer at a participating LGBTQ community center or be in the referral network of a participating LGBTQ community center (i.e., receive referrals or intending to receive referrals of mental health clients from the center). Mental health providers will be recruited by center leadership. Upon randomization, center leaders will distribute flyers to their employees, volunteers, and referral network providers to inform them of the study/training opportunity. Center directors will be asked to share information about the benefits of the study/training (e.g., continuing education credits, free training materials, financial incentive for assessments).

To be eligible to attend the training, mental health providers must provide consent and complete the baseline survey. Upon training launch, enrolled providers will be given instructions on how to access their respective training materials and, if applicable, live webinar training sessions. Regardless of their engagement with their respective training intervention or whether they remain affiliated with an LGBTQ community center, all providers will be contacted to complete follow-up surveys at 4-, 8-, 12-, and 24-months post-baseline. No concomitant interventions are prohibited for mental health providers enrolled in the trial.

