#### Local supervision

Four weeks after the final direct training session, the 30 centers randomized to the Local Supervision condition will send their nominated local supervisors to the first of 12 remote leadership workshop sessions focused on LGBTQ-affirmative supervision, training, and sustainment. In the train-the-trainer format to be employed in the Local Supervision condition, expert clinicians will provide additional training to local supervisors with the goal of increasing their ability to train other local mental health providers into the future. This training strategy has the benefit of harnessing local expertise, potentially making LGBTQ-affirmative CBT more responsive to local realities [85–87]. The goal of the LGBTQ-affirmative CBT leadership workshop is to provide local supervisors at LGBTQ centers with the tools, skills, and knowledge to become leaders and experts in LGBTQ-affirmative CBT and to train and supervise mental health providers at their center in LGBTQ-affirmative CBT for sustainment of this practice locally. Participants will receive email reminders about the training. Engagement and adherence will be monitored weekly.

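### On the post-baseline schedule, the 4-month mediators precede nearly all of the Local Supervision component and say little about how it differs from Direct Training

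*Protocol article*

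**What the plan says.** **Mediator timing.** In the protocol article, Mediation analyses, the effect of strategy on 8-month fidelity is split "through our hypothesized organizational and provider targets measured at 4-month follow-up". Two mixed models are fitted: the first adjusts for baseline targets, and "the second model replaces baseline organizational and provider targets with 4-month follow-up targets". The indirect effect is the difference between the two strategy coefficients. The client model, for PHQ-9 at 12 and then 24 months, makes the same swap, and in addition "baseline implementation fidelity is replaced with 8-month follow-up implementation fidelity".

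**What separates the arms.** Under Materials only and Direct training, both of the more intensive arms receive the online platform, the manual and 12 weekly webinars. The section Local supervision then says: "Four weeks after the final direct training session, the 30 centers randomized to the Local Supervision condition will send their nominated local supervisors". What these supervisors start at that point is the leadership workshop, which has 12 sessions. The Abstract describes this arm as "the above plus one year of supervision from a local supervisor". The article does not say when that year begins.

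**Survey anchor.** Under Mental health providers, "all providers will be contacted to complete follow-up surveys at 4-, 8-, 12-, and 24-months post-baseline". The Directors, Clients and Outcomes sections use the same anchor, and providers must complete the baseline survey before they may attend training. The Background instead hypothesizes "graduated increases in implementation success at 4-, 8-, 12-, and 24-months post-training".

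**Maintenance.** Under Provider implementation fidelity outcome analyses: "We will re-run these analyses with 12- and 24-month outcomes to determine implementation maintenance".

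**The concern.** A mediator can carry the effect of a strategy only if it is measured after that strategy has had a chance to act. Until the first workshop session, the article describes no difference in training content between Local Supervision and Direct Training. If the 4-month survey falls about when the workshop starts, the two arms should have nearly the same targets at that wave.

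This matters because the Background hypothesizes that organizational and provider factors mediate the stronger impact of the more intensive strategies, and Aim 3 is built on that hypothesis. Supervision competency shows the problem most plainly. Table 1 lists it as an organization-level target, the workshop exists to raise it, and the mediation models would read it when the workshop has barely begun. A null for this contrast could then be reported as evidence against the mechanism when it reflects only the measurement date.

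Two related timing matters affect interpretation. The hypothesis and the Methods use different anchors for every follow-up wave, including the 8-month primary endpoint. And a 12-month result is labelled maintenance although one arm may still be receiving its year of supervision.

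**Working it through.** The plan states no figure for mediation power or exposure, so there is none to reproduce. The check is calendar arithmetic.

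**Inputs.**
- 12 weekly webinars (Direct training).
- Workshop session 1 four weeks after the last webinar (Local supervision); 12 sessions over 12 weeks (Local supervisors).
- Surveys at 4, 8 and 12 months after baseline (Outcomes).
- Gap *g* in weeks between baseline and training launch: not stated. It is assumed to lie between 0 and 8.

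**Conversion.** Weeks per month = 365.25 / 12 / 7 = 4.348. So 4 months = 17.4 weeks, 8 months = 34.8 and 12 months = 52.2.

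**Workshop dates, in weeks from launch.** If the first webinar is at week 0, the last is at week 11, session 1 is at 11 + 4 = 15 and session 12 is at 15 + 11 = 26. If the last webinar is counted at week 12, these become 16 and 27.

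**Sessions held by a survey at *t* weeks post-baseline.** With session 1 at week *s*, the number is floor(*t* − *g* − *s*) + 1, limited to 0–12, and zero if *t* − *g* < *s*.

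| Gap *g* (weeks) | By month 4, *s* = 15 | By month 4, *s* = 16 | By month 8, *s* = 15 | By month 8, *s* = 16 |
|---|---|---|---|---|
| 0 | 3 | 2 | 12 | 12 |
| 1 | 2 | 1 | 12 | 12 |
| 2 | 1 | 0 | 12 | 12 |
| 3 | 0 | 0 | 12 | 12 |
| 4 | 0 | 0 | 12 | 12 |
| 6 | 0 | 0 | 12 | 12 |
| 8 | 0 | 0 | 12 | 11 |

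Example: *g* = 0 and *s* = 15 give 17.4 − 15 = 2.4, so three sessions. With *g* = 8 and *s* = 16, month 8 gives 34.8 − 8 − 16 = 10.8, so 11 sessions.

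**Effect on the estimate.** In a linear model the coefficient difference is roughly *a* × *b*, where *a* is the difference between the arms in the 4-month target and *b* is the association of that target with the outcome. If the arms have barely diverged by month 4, *a* is small whatever the value of *b*. An effect that reaches 8-month fidelity through targets changing between months 4 and 8 then stays in the second model's strategy coefficient, which the plan reads as direct.

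**Other anchor.** If 4 months runs from the last webinar, the survey falls at week 11 + 17.4 = 28.4 or 12 + 17.4 = 29.4. Both come after session 12, so the mediator problem disappears. The two anchors differ by 11–12 weeks plus any gap, which is about three months at every wave.

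**Maintenance.** If supervision starts at launch, its year ends at week 52.2 + *g* post-baseline, which is month 12 or later. If it starts with the workshop and *g* = 0, then 52.2 − 15 = 37.2 weeks (or 52.2 − 16 = 36.2) of the year have passed at month 12.

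**The case against.** A reader might infer that the mediation analysis cannot detect any difference between Local Supervision and Direct Training, or that Aim 3 will report no mediation whatever the truth. The documents do not support that, for three reasons.

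- The PHQ-9 model also swaps in 8-month fidelity, measured when 11–12 of 12 sessions have been held. That term contributes to the coefficient difference, so an indirect path through fidelity remains open at 12 and 24 months.
- Supervisors are nominated upon randomization and the start of supervision is not stated. Naming a local lead could move implementation climate or leadership before the workshop. A small 4-month difference is likely; a difference of zero is not shown.
- Under the Background's post-training anchor the problem vanishes. But four sections use post-baseline, and the Materials Only arm is self-paced, so post-training has no common date across the arms. This leaves a wording conflict to resolve and does not rescue the 4-month targets as the Methods now time them.

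It is also fair that the primary fidelity comparison is untouched, that the section on mediators describes the serial mediation as exploratory, and that the 24-month analyses are already planned. For PHQ-9 mediation the plan already reserves maintenance for 24 months. These points limit how much rests on the problem. They do not make the 4-month targets informative for this contrast, and the Background and Mediation analyses do state mediation as a hypothesis.

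**Conclusion.** The concern holds in limited form. On the post-baseline anchor, the 4-month targets are read after 0–3 of 12 workshop sessions, so mediation of Local Supervision versus Direct Training through them is largely uninformative. This applies in full to the 8-month fidelity mediation, and to the part of the PHQ-9 mediation that runs through the targets themselves. Direct Training versus Materials Only is not affected.

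The conclusion rests on the post-baseline anchor and on the workshop being the main point at which the two arms diverge. It does not depend on the unstated gap: no gap is the most favourable case, and even then at most a quarter of the sessions have been held.

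The maintenance point is one of interpretation. It holds if supervision starts no earlier than training launch, which the article neither says nor rules out.

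**What to change.** 1. **Add a mediation analysis for Local Supervision versus Direct Training.** Prespecify 8-month targets with 12-month fidelity, and 8-month targets plus 12-month fidelity with 24-month PHQ-9. Table 1 already collects the targets and fidelity at these waves. Fidelity has to move to 12 months here, because 8-month targets with 8-month fidelity would lose temporal order. Keep the planned analyses of 8-month fidelity and 12-month PHQ-9 alongside, and state that a null through the 4-month targets will not be read as absence of mediation for this contrast.

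2. **Use one anchor.** Reconcile the Background's post-training wording with the post-baseline wording in the Methods and Outcomes. If post-training is what was meant, item 1 is not needed, but the date from which a self-paced arm is followed must then be defined.

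3. **Limit the maintenance label.** State when the year of supervision begins. For contrasts involving Local Supervision, interpret only the 24-month result as maintenance.

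**Cost.** No new data are needed; the changes are to analysis wording, plus one added set of models. The added analysis explains an outcome later than the 8-month primary endpoint and will suffer more attrition. That is a real limit for clients: there are five centers per arm, and the power calculation already assumes 25% loss for the 8-month outcome. For this reason it should supplement the planned mediation and not replace it.

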### Randomization

Upon receiving 90 signed memoranda of understanding, the 90 LGBTQ community centers will be randomized in a 1:1:1 ratio to receive one of the three implementation strategies. Randomization will be stratified by director report of anticipated staff participation. Specifically, high-attendance centers will be operationalized as those with greater than the median number of anticipated providers across the 90 enrolled centers whereas low-attendance centers will be operationalized as those that anticipate fewer than the median number of providers per center. Centers whose anticipated number of providers is at the median will be randomly and evenly divided across the two groups. The 15 effectiveness centers will be randomized separately to ensure their equal distribution across the three implementation strategies. Randomization allocation will be generated by the study statistician and assigned by the study coordinator. All participants and study staff will be unmasked to condition assignment, as necessitated by the study design.

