##### Sample size justification

Provider implementation fidelity serves as our primary outcome used to estimate sample size given its role in linking provider behavior to client mental health [84, 94–96]. We estimate that approximately six mental health providers will enroll per center, or about 540 providers total. Power was computed to test the null hypotheses of no difference between Materials Only and Direct Training and between Direct Training and Local Supervision in a cluster trial. For the primary implementation outcome, the change from baseline to 8-month follow-up was estimated as 0.14 for the Direct Training strategy and its variance was estimated as 0.0439 using data obtained from the waitlist-controlled trial [57]. Thus, the standardized change for the Direct Training strategy was estimated at 0.67. With a 0.025 Type I error rate, allowing for two primary comparisons between the three strategies, we will have 80% power to detect an effect of *d* = 0.34–0.46 on the 8-month change of the primary outcome, assuming a between-center ICC ≤ 0.1. In other words, we will have 80% power to detect the difference between Materials Only and Direct Training when the standardized change for Materials Only is ≤ 0.21–0.33, and we will have 80% power to detect the difference between Direct Training and Local Supervision when the standardized change for the Local Supervision strategy is ≥ 1.01–1.13.

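### The mediation analysis takes a coefficient difference between non-nested models, so the indirect effect is biased whenever the dropped baseline target still predicts the outcome and the strategy moves the target

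*Protocol article*

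**What the plan says.** The Mediation analyses section of the protocol article specifies both models and the estimator.

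- **Estimator:** "The indirect effect is the difference between the estimated coefficients of implementation strategies between the two models", with significance tested by bootstrapping.
- **Fidelity at 8 months, first model:** "The fixed effects of the first model include the implementation strategies, baseline implementation fidelity, and baseline organizational and provider targets".
- **Fidelity at 8 months, second model:** "the second model replaces baseline organizational and provider targets with 4-month follow-up targets". Baseline fidelity stays in.
- **PHQ-9 at 12 months (rerun at 24), second model:** "the baseline organizational and provider targets are replaced with 4-month follow-up targets", and "baseline implementation fidelity is replaced with 8-month follow-up implementation fidelity". Baseline PHQ-9 is not among the replaced terms.

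An earlier sentence in the same section describes the second model as the strategies with the targets added. The detailed specification that follows departs from this, and nothing elsewhere in the article puts the baseline targets back. The covariates of both models are thus stated choices, not detail left to a later analysis plan.

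**The concern.** A difference in coefficients isolates mediation when the mediators are the only thing that changes between the models. Here the baseline adjustment changes too.

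The second model is also where the baseline target matters most. Randomization protects the comparison of strategies, but not the relation between the 4-month target and the outcome. A center or provider that scored high on a target at baseline is likely to score high at 4 months, and may have better outcomes for other reasons. Once the baseline score is dropped, that association is credited to the 4-month target and so to mediation.

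Mechanism is part of Aim 3, and mediation is stated as a hypothesis in the Background. A distorted indirect effect would bear directly on that claim.

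**Working it through.** The protocol states no figure for the mediation analyses, so there is none to reproduce.

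**Inputs from the protocol.** Randomization: "the 90 LGBTQ community centers will be randomized in a 1:1:1 ratio", so 30 centers per arm. Sample size for fidelity: "approximately six mental health providers will enroll per center", with a between-center ICC up to 0.1. PHQ-9 subset: 15 centers, five per arm, at least 52 clients each and 25% loss, so 52 × 0.75 = 39 retained.

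**Assumed inputs.** All effect sizes below are assumptions, in SD units.

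**Set-up.** Let T be the strategy (two adjacent arms), M0 and M4 the baseline and 4-month target, and Y the outcome:

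- M4 = a·T + ρ·M0 + error
- Y = c·T + b·M4 + g·M0 + error

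The true indirect effect is a·b. The term g is what the baseline target still says about the outcome once M4 is known.

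**Bias.** Omitting M0 from the second model changes the M4 slope from b to b + g·s, where s is the slope of M0 on M4 given the other covariates. The planned difference is then a·(b + g·s), so the bias is a·s·g. With M0 and M4 scaled to SD 1 within arm and no other correlated covariate, s = ρ.

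For a = 0.5 and b = 0.3 (true value 0.15), the relative bias is:

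| ρ | g = 0 | g = 0.1 | g = 0.2 | g = 0.3 |
|---|---|---|---|---|
| 0.3 | 0 | +10% | +20% | +30% |
| 0.5 | 0 | +17% | +33% | +50% |
| 0.7 | 0 | +23% | +47% | +70% |

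Keeping M0 in both models gives zero bias in every cell.

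**Example with baseline fidelity in both models.** Take a = 0.5, ρ = 0.6, residual SD of M4 0.8, g = 0.3, and a correlation of 0.4 between baseline fidelity and M0.

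- Variance of M0 given baseline fidelity: 1 − 0.4² = 0.84.
- s = (0.6 × 0.84) / (0.36 × 0.84 + 0.64) = 0.504 / 0.9424 = 0.535.
- Bias: 0.5 × 0.535 × 0.3 = 0.080.

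Simulation of this setting (2,000 trials, 30 centers × 6 providers per arm, fixed effects only) agrees:

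| True indirect effect | g | As planned | Baseline kept |
|---|---|---|---|
| 0 | 0.3 | 0.08 | 0.00 |
| 0.10 | 0.3 | 0.18 | 0.10 |
| 0.10 | −0.2 | 0.05 | 0.10 |
| 0.10 | 0 | 0.10 | 0.10 |

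In the first row the total effect is 0.30, so 0.08 / 0.30 = 27% would be reported as mediated when none is.

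**Random center effects.** With a random intercept, ICC 0.1, a = 0.5, ρ = 0.5 and g = 0.2 (4,000 replicates), the planned estimate averages 0.198 against 0.149 with baseline kept, for a true 0.150. With b = 0 the averages are 0.050 and 0.000.

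**Chance imbalance.** If a = 0, the planned estimate averages zero but is noisier. At b = 0, g = 0.2 and ρ = 0.5, a 1-SD baseline imbalance shifts it by −g(1 − ρ²) = −0.2 × 0.75 = −0.15, against about 0 with baseline kept. Its SD is 0.023 against 0.005. For a center-level target the SD of the imbalance is √(2/5) = 0.63 with five centers per arm, and √(2/30) = 0.26 with 30.

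**Fifteen centers, one center-level target** (a = 0, ρ = 0.6, ICC 0.01, 39 clients per center), SD of the estimate:

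| g | b | As planned | Baseline kept |
|---|---|---|---|
| 0.3 | 0 | 0.163 | 0.035 |
| 0.1 | 0.2 | 0.148 | 0.114 |
| 0 | 0.2 | 0.113 | 0.113 |

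**Fifteen centers, five center-level targets.** Table 1 lists up to five organizational measures: three Implementation Climate subscales, the leadership scale and supervision competency. Entered at both times they need 1 + 2 + 5 + 5 = 13 center-level parameters for 15 centers; the planned second model needs 1 + 2 + 5 = 8. The SD is then 0.150 as planned against 0.325 with all baselines kept (g = 0.06, b = 0 for each target).

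**The case against.** Several objections have force.

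- **The bias is conditional.** A reader might infer that the planned indirect effect is always biased. The protocol does not support that: if the baseline target acts only through its 4-month value, g = 0 and the two versions agree. But the protocol neither states nor justifies that special case, and error in survey-measured targets makes it unlikely, because the baseline score then still carries information about the true target.
- **Chance imbalance is not bias.** A reader might infer that dropping baseline creates false mediation even when the strategy leaves the target alone. Under randomization this part averages zero, and a bootstrap that resamples centers would carry the noise into the interval. This stands. Bootstrapping does not repair the other part: it tests whether the coefficient difference is zero, whatever makes it nonzero.
- **The noise gap at 15 centers is easily overstated.** The more than fourfold gap (0.163 against 0.035) needs one target, a large residual baseline effect and a target with no effect on the outcome. With g = 0 there is no gap. With five targets, keeping every baseline term roughly doubles the noise. This stands and limits the remedy.
- **The analysis is secondary.** The section on implementation and effectiveness mediators speaks of exploring serial mediation, and the primary analyses do not use these models. This stands for severity. It does not remove the point, because Aim 3 names mechanisms.

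**Conclusion.** The point holds in conditional form. As specified, the indirect effect is a difference between non-nested models, with a large-sample bias of about a·s·g. That bias is present when the strategy moves the target and the baseline target predicts the outcome beyond its 4-month value. It inflates or shrinks the estimate according to the sign of g, and is zero when g = 0. Where the strategy does not move the target, the harm is extra variance only.

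The size cannot be fixed from the protocol. Across the assumed values tabulated, the bias runs from none to 70% of a true effect of 0.15, and an effect of 0.08 can appear where none exists. The PHQ-9 mediation is more exposed, since baseline fidelity is dropped as well and there are only five centers per arm.

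This should be corrected, but it does not threaten the trial's main results: the primary fidelity and PHQ-9 comparisons and their sample sizes are untouched.

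**What to change.** **Fidelity mediation, 90 centers.** Keep baseline fidelity and the baseline organizational and provider targets in both models, and add the 4-month targets to the second model instead of substituting them.

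**PHQ-9 mediation, 15 centers (12 and 24 months).** Use the same nested structure: baseline PHQ-9, baseline fidelity and baseline targets in both models, with the 4-month targets and 8-month fidelity added in the second. Test the organizational targets one at a time or as a small composite set fixed in advance. One target needs 1 + 2 + 1 + 1 = 5 center-level parameters instead of 13.

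**Cost.** A short change of wording, with no new data for the targets, fidelity or PHQ-9, since Table 1 already schedules them at baseline and follow-up. Some degrees of freedom are lost in the 15-center model. Testing targets singly also means that the separate indirect effects cannot be added up as shares of one total.
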